### 3.7. Blinding and Blind Rating

Due to the nature of the intervention (a dynamic seat), children, parents and the visiting occupational therapist will not be blinded to the randomised baseline period allocation. The investigators will assess all children before randomisation takes place. Primary outcome measures will be administered and videoed by a member of the research team. Raters of these video-recorded assessments will be blind to the time of assessment.

Research therapists will assess all children at each assessment time point, using video, with subsequent ratings performed by trained blind assessors. Primary and secondary outcome measures will be videoed for subsequent rating by trained independent raters, blind to the time of assessment in relation to treatment. The order of video segments will be randomised before being collated for rating. Metadata, including date, will be removed from the videos to maintain blindness.

### 3.8. Intervention to Be Studied

The KiTE 2 whole-body dynamic seat is designed for children with dystonic cerebral palsy [14]. It combines postural support and maintains lateral spinal alignment in the child, while also allowing substantial extension of the hips, knees and ankles should the child experience an involuntary dystonic movement or choose to move voluntarily. The seat is able to accommodate asymmetric movements as each leg is supported and able to move independently of the other and of the backrest. There is no mechanism linking the movements of the backrest and leg supports. The joints of the seat are pivoted anatomically, with each pivot point in the seat being aligned with the pivot points of the child’s own joints.

### 3.9. Assessments

Baseline assessments and outcome measures will use multi-dimensional assessments across the ICF [2]. Measures of impairment, activity and participation will be used for sample description, outcome evaluation before and after intervention and at follow up two months after the conclusion of the intervention period. Assessments at intake will not be repeated post intervention. Validation of outcome measures in dystonia is limited with most assessments used in trials having been validated for other populations [15]. As this is a feasibility study, some of the feasibility parameters as per the National Institute for Health Research (NIHR) are: (i) to calculate the standard deviation of the primary outcome measure needed to estimate sample size on a future large scale trial and (ii) to explore characteristics of the proposed outcome measures [16]. Whilst some studies including children and young people with dystonia have explored the use of outcome measures such as as the Canadian Occupational Performance Measure (COPM) [17], and the Performance Quality Rating Scale [18], also proposed in this study [19,20] they evaluated neurosurgical and rehabilitation interventions. The possibility of applying those outcome measures to evaluate functional improvement in younger children with dystonia following provision of specialist equipment is unknown and this feasibility study will explore their application and whether changes to implementation are required. Reliability and Validity of these measures when applied to dystonic movement disorders can be therefore explored at posteriori.

### 3.10. Primary Outcomes

There will be three primary outcome measures. Two complementary co-primary objective outcome measures will be employed: the first one will be a subjective rating scale to explore parents/carers perceived performance and satisfaction on a number of self-selected goals using the Canadian Occupational Performance Measure (COPM) [17]. Secondly, the Performance Quality Rating Scale (PQRS) [18] will be used to measure the individual goals selected for the intervention and will be blind-rated. Further, seating tolerance will be objectively measured using sensors attached to the chair that will capture the duration and frequency of its use throughout the baseline and intervention and follow-up periods.

### 3.11. Secondary Outcomes

There will be four secondary outcomes. The first one, The Responsive Augmentative and Alternative Communication Style Scale (RAACS), will be used to measure interaction between a parent or carer, and the child at pre-intervention, post-intervention, and 2 month follow up. The second one, Paediatric Quality of Life Inventory (PedsQL), will rate the levels of difficulty in a number of areas. The third one will measure the upper limb reach. The fourth one will measure the sleep quality.

### 3.12. Baseline Assessments for Treatment Planning

One assessment will be used to establish goals for intervention: COPM [17]. This assessment will also be used as outcome measure

### 3.13. Other Demographic and Clinical Measures

Demographic measures (age, gender, etc.) will be used for descriptive purposes. The Burke–Fahn–Marsden Dystonia Rating Scale (BFMDRS) [21] will be used to evaluate dystonia severity following the published protocol.

Functional motor abilities will be classified using the Gross Motor Classification System (GMFCS) [12] and the MACS/mini-MACS [13,22]. These ordinal scales have been validated for use with children with CP and the levels provide information about limitations in daily life with higher scores implying more functional difficulties. The use of these scales for children with other conditions other than CP has been described as GMFCS and MACS equivalents. This does not require involvement of the children or families and it is a classification system that can be done after observing the children move and handle objects and through the information gathered on other assessments explained below.

### 3.14. Description of Standard Care

Participants will be randomised to length of baseline and the same measurements will be acquired during this period when the child will be using their usual static seating system (chair). As the provision of static seating tends to differ across the country, we will capture this data as part of the feasibility parameters captured. We will record other type of standard care that participants receive including occupational therapy, physiotherapy and any other early intervention.

### 3.15. The Seat Intervention

The specifically designed dynamic seating system will be set-up by a qualified occupational therapist/physiotherapist and an engineer from the study team. The intervention (dynamic chair provision) will consist of a trial of 8 weeks. Figure 1 shows the seat model that will be trialled. A researcher will visit the child and family once per week to measure goals set up by the family. This, in itself, could be considered an intervention as the family might not have set clear goals if they were not involved in the trial. These visits will be video recorded for subsequent scoring and review.

### 3.16. Inter- and Intrarater Reliability

Reliability training will be required for the independent assessors. For initial training, the raters use videos from the CMDS database and live assessments of a number of consecutive children. An interclass correlation coefficient ≥0.8 between raters and within raters over repeat tests will be required before a rater is able to continue. The ICC will be calculated for the primary outcome measure, the Performance Quality Rating Scale (PQRS) [18]. At the end of the trial, raters will be re-assessed on the training videos to ensure there has been no rating drift.

### 3.17. Assessment Time Points (Data Collection)

Table 1 shows the study timeline and participant journey for assessment time points and data collection. Figure 2a,b are flow charts describing the processes for the baseline and intervention periods in the study and should be read in conjunction with Table 1.

#### Outcome Evaluation

Primary and secondary outcome measures across activity and participation domains will be completed at baseline (b1–b7, with baseline length randomly allocated), during intervention (for repeated measures such as PQRS, sensor based data and accelerometers) (t1–t8), post intervention (p1, p2) and follow up (f1, f2) and include the COPM, PQRS, seat occupancy, RAACS, Peds-QL, time to target, path complexity, reaching performance and sleep quality.

Response will be tracked using multiple video recordings during sessions of goals identified for intervention as well as with sensor data and data from accelerometer. The Performance Quality Rating Scale (PQRS) will be used for goals, and sensor data for seat occupancy, and frequency and intensity of movement in bed as an indicator of sleep quality. Data points will be collected at baseline (b1–b7), during intervention (t1–t8); post-intervention (p1) and 2 month follow up (f2). There will be a minimum of 3 video-recorded baseline assessments of each goal before intervention and minimum of 3 trials post intervention and at 2 months review. Further, outcome evaluation measures outlined above will be completed at t1 and t2. The PQRS will be rated by an independent observer using video recordings. The videos from baseline, post-test and follow up will be presented in a randomized non-chronological order. A third party will complete assessments at baseline and post treatment. PQRS will be scored blinded by another occupational therapist using video recordings randomly presented.

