### 3.18. Sensor-Based Measurements

**Seat occupancy profile:** This will be measured continuously at baseline, during and after the intervention periods, using a simple pressure switch and data logger attached to the participant’s seat. The data logger will record when and for how long the seat is occupied. The system requires no intervention from the participant or their family between setup and removal.

**Sleep quality:** This will be measured using a simple lightweight inertial measurement unit (IMU) attached to the child using a wrist or ankle band. This measurement has been trialed with children during the previous and preparatory KiTE 1 project [23]. Parents will be asked to ensure that their children wear the sensor band for at least 2 nights per week during the baseline and intervention periods. The sensors require no intervention by the parent other than placing the sensor on the child’s wrist or ankle and switching it on when they go to bed.

**Daytime activity intensity and frequency:** To be measured using the IMUs for 2 days per week, preferably two days either side of a measured night. The sensors will be used to measure how much the child moves, and the intensity and duration of their movement.

Sensor data collection and analysis is shown on Table 2. It will be collected by a study researcher during weekly visits to the participant and transferred to secure encrypted storage using the project laptop. Data will be coded and pseudonymised on collection.

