### 3.19. Data Analyses Plan

A full statistical analysis plan for the study will be available. Descriptive statistics will be used to summarise demographic characteristics of the participants, including age and diagnosis. Functional ability will be classified using GFMCS and MACS/Mini-MACS.

Primary and secondary outcome measures across the domains of the ICF will be completed at baseline, post-intervention and follow up. There will be two types of data depending on whether the within- or between-subjects data are examined. Within subject data will evaluate the SCED data with direct replications. Between-subjects evaluation for outcome measures pre-intervention, post-intervention and follow up will be used for all measures calculating means and 95% confidence intervals for overall change. There is no planned interim analysis.

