**ASSESSMENTS**																							
GMFCS	X																						
mini-MACS/MACS	X																						
Demographics	X																						
BFMDRS (Dystonia)	X																		X				
**TIMEPOINT**	e1	b1	b2	b3	b4	b5	b6	b7	c1	c2	t1	t2	t3	t4	t5	t6	t7	t8	p1	p2	f1	f2	cc1
PQRS (Task Performance)		xxx	xxx	xxx	xxx	xxx	xxx	xxx			xxx	xxx	xxx	xxx	xxx	xxx	xxx	xxx	X				
COPM (Goal Attainment)		X																		X		X	
Seat Occupancy (Sensor)		X	X	X	X	X	X	X			X	X	X	X	X	X	X	X		X		X	
RAACS (Communication)		X																		X		X	
Sleep Quality (Sensor)		X	X	X	X	X	X	X			X	X	X	X	X	X	X	X					
QoL (PedsQL)		X																		X		X	

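### Sleep quality is scheduled at p1 and f2 in Section 3.17 but not in Section 3.18 or Table 1, leaving its between-subjects post and follow-up summary without data if the latter two are followed

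*Protocol article*

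**What the plan says.** Section 3.11 lists four secondary outcomes, of which "The fourth one will measure the sleep quality".

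Section 3.17 (Outcome Evaluation) places sleep after the intervention in two ways. Its first paragraph gives a pooled list of outcomes for baseline, intervention, "post intervention (p1, p2) and follow up (f1, f2) and include the COPM, PQRS, seat occupancy, RAACS, Peds-QL, time to target, path complexity", and the list ends with "reaching performance and sleep quality". Its second paragraph names the repeatedly tracked measures: PQRS, seat occupancy, and "frequency and intensity of movement in bed as an indicator of sleep quality". The next sentence sets their time points: "Data points will be collected at baseline (b1–b7), during intervention (t1–t8); post-intervention (p1) and 2 month follow up (f2".

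Section 3.18 describes the sleep sensor. Parents are to have the child "wear the sensor band for at least 2 nights per week during the baseline and intervention periods". The same section has seat occupancy recorded after the intervention as well.

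In Table 1, the row "Sleep Quality (Sensor") is marked at b1–b7 and t1–t8 and nowhere else. The table note explains that an X shows when an assessment takes place.

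Section 3.19 names two strands of analysis. One is a within-subject evaluation of the single-case data. The other is: "Between-subjects evaluation for outcome measures pre-intervention, post-intervention and follow up will be used for all measures", giving means and 95% confidence intervals.

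**The concern.** The text and the operational schedule disagree on whether sleep is recorded once the 8 intervention weeks end. Families and visiting staff will work from the band instruction and the visit table. If they do, no sleep nights are recorded at post-intervention or follow up, although Section 3.19 promises a summary at both points for all measures.

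Such a gap would come from the schedule itself. It would affect every child alike, and no analysis could recover it afterwards. At stake are one part of the analysis of a secondary outcome and any statement about sleep two months after the intervention.

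**Working it through.** The plan gives no figure to reproduce. The check compares the places that fix the sleep time points.

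| Place | Baseline | t1–t8 | Post | Follow up |
|---|---|---|---|---|
| 3.17, first paragraph (pooled list) | yes | yes | p1, p2 | f1, f2 |
| 3.17, second paragraph | b1–b7 | t1–t8 | p1 | f2 |
| 3.18, sleep band | yes | yes | not requested | not requested |
| Table 1, sleep row | 7 marks | 8 marks | 0 of 2 columns | 0 of 2 columns |
| 3.19, between-subjects summary | needed | not named | needed | needed |

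**Does the key sentence cover sleep?** In 3.17, second paragraph, it directly follows the sentence naming PQRS, seat occupancy and movement in bed. It therefore covers sleep.

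**Are the blank cells a reading error?** The sleep row lines up with the header: e1 blank, b1–b7 marked, c1 and c2 blank, t1–t8 marked, then p1, p2, f1, f2 and co1 blank. That is 7 + 8 = 15 marks. The seat occupancy, COPM, RAACS and PedsQL rows keep marks at p2 and f2, so those columns were read correctly. The blanks also agree with the wording of 3.18.

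**What is lost under 3.18 and Table 1.** The between-subjects summary needs 3 time points × 6 children = 18 child-by-time-point cells. Sleep fills 1 × 6 = 6 of them (pre-intervention) and leaves 2 × 6 = 12 empty.

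**What remains under 3.18 and Table 1.** At the stated minimum of 2 nights per week, each child gives 2 × 2 = 4 to 2 × 7 = 14 baseline nights, depending on the randomised baseline length, and 2 × 8 = 16 intervention nights. That is 20 to 30 nights per child, in both phases of the within-subject comparison.

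**What is lost under 3.17.** Nothing: p1 and f2 supply the two later time points.

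**The case against.** A reader might infer that the planned sleep analysis as a whole cannot be done. The documents do not support that. Section 3.19 names a within-subject strand first, and Section 3.1 makes each child's usual-seating phase against the dynamic-seat phase the core comparison of the design. Sleep has weekly data in both phases. Section 2.3 asks only whether changes can be observed in the secondary outcomes, so persistence of a sleep change is not a stated aim.

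A reader might also infer that Section 3.18 forbids later band wear. It does not: it sets a minimum for two periods and does not exclude others. The exclusion is inferred from the blank Table 1 cells and from the contrast with seat occupancy, which the same section extends beyond the intervention. The inference is reasonable, but it remains an inference.

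The first paragraph of 3.17 is weak evidence. It pools measures, and it also attaches COPM, RAACS and PedsQL to b1–b7, where Table 1 gives each of them b1 alone at baseline. The conflict therefore rests mainly on the second paragraph of 3.17 and on the coverage of all measures in 3.19.

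Nor is sleep the only mismatch. The Table 1 PQRS row ends at p1 although 3.17 requires trials at the 2 month review, and occupancy is at p2 in Table 1 but p1 in 3.17. That argues for one pass over the whole schedule. It does not remove the sleep conflict.

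Finally, a separate analysis plan could define t8 nights as the post value. This article does not say so, and no analysis plan can supply follow-up nights that were not recorded.

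**Conclusion.** The concern holds as an internal contradiction with a limited consequence. If Section 3.18 and Table 1 are followed, the between-subjects post-intervention and follow-up summary of sleep cannot be computed for any of the 6 children (12 of 18 cells empty), and the trial can say nothing about sleep at follow up. The within-subject comparison of baseline weeks with t1–t8 stands in full.

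This size is conditional. It assumes that staff and families follow the band instruction and the visit table rather than 3.17, that a blank Table 1 cell means no assessment, and that t8 nights are not redefined as the post value. If 3.17 is followed, nothing is lost. Power, effect size and sample size play no part in the point.

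**What to change.** Reconcile 3.17, 3.18, Table 1 and 3.19 in one of two ways.

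1. **Collect the data.** Add at least 2 nights of band wear around the post-intervention visit and at least 2 around f2 to Section 3.18, and mark the Table 1 sleep row to match. State whether the post value belongs to p1 or p2. The cost is about 2 + 2 = 4 nights per child on top of the existing minimum of 20 to 30, or 4 × 6 = 24 nights over the series. The band must also stay with the family after t8 or be returned to them, which the article does not now provide for.
2. **Restrict the analysis.** Remove sleep from the post-intervention and follow-up lists in 3.17, and state in 3.19 that sleep is analysed only as baseline weeks versus t1–t8. This costs wording only, but gives up any statement on sleep at follow up.

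Section 4 reports that recruitment has not begun, so either change can be made before any nights are lost. The PQRS and seat occupancy rows should be checked against 3.17 in the same revision.

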### 3.18. Sensor-Based Measurements

**Seat occupancy profile:** This will be measured continuously at baseline, during and after the intervention periods, using a simple pressure switch and data logger attached to the participant’s seat. The data logger will record when and for how long the seat is occupied. The system requires no intervention from the participant or their family between setup and removal.

**Sleep quality:** This will be measured using a simple lightweight inertial measurement unit (IMU) attached to the child using a wrist or ankle band. This measurement has been trialed with children during the previous and preparatory KiTE 1 project [23]. Parents will be asked to ensure that their children wear the sensor band for at least 2 nights per week during the baseline and intervention periods. The sensors require no intervention by the parent other than placing the sensor on the child’s wrist or ankle and switching it on when they go to bed.

**Daytime activity intensity and frequency:** To be measured using the IMUs for 2 days per week, preferably two days either side of a measured night. The sensors will be used to measure how much the child moves, and the intensity and duration of their movement.

Sensor data collection and analysis is shown on Table 2. It will be collected by a study researcher during weekly visits to the participant and transferred to secure encrypted storage using the project laptop. Data will be coded and pseudonymised on collection.

### 3.19. Data Analyses Plan

A full statistical analysis plan for the study will be available. Descriptive statistics will be used to summarise demographic characteristics of the participants, including age and diagnosis. Functional ability will be classified using GFMCS and MACS/Mini-MACS.

Primary and secondary outcome measures across the domains of the ICF will be completed at baseline, post-intervention and follow up. There will be two types of data depending on whether the within- or between-subjects data are examined. Within subject data will evaluate the SCED data with direct replications. Between-subjects evaluation for outcome measures pre-intervention, post-intervention and follow up will be used for all measures calculating means and 95% confidence intervals for overall change. There is no planned interim analysis.

#### 3.19.1. Data from SCED

To describe the impact of the intervention in the single-case experimental studies, pre-intervention and post-intervention raw scores will be examined in all outcome measures. Analysis of PQRS changes will be evaluated using an appropriate analysis for SCED. The analysis will be guided by interpretation of the visual representation of the results; whether there is auto-correlation on baseline data; and whether there is baseline trend present in the data set. We will follow the recommendations from the Single-Case Reporting Guideline in Behavioural Interventions (SCRIBE) [24]. Visual analysis will be undertaken to evaluate changes in the domains of means, levels, trends, variability, latency and consistency. This will be followed by statistical analysis of the graph which will vary depending on serial dependency. Estimated effect size will be calculated using a suitable regression approach for SCED. We will initially fit a naïve linear regression model using ordinary least squares for reference only. We will use the Tau-*U* approach as it takes into account baseline trend and is considered one of the most robust effect size methods in SCED [25].

SCED uses repeated measures and therefore provides multiple data points. The extended baseline and intervention phases will result in many data points. PQRS can be applied multiple times within the same practiced task, given it is scoring the quality of performance rather than one-off task performance [20]. Therefore, each task step within a task is assigned a data point.

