## 3. Method

### 3.1. Design

The proposed study design is a series of N-of-1 trials, with replications across subjects (N-of-1 plus 5 replications). For each child, there will be at least 5 baseline assessments over at least 2 weeks in their usual seating (each trial provides one data point or baseline assessment, for example, reaching forward to hit a switch is one data point/one baseline). Therefore, there will be multiple baselines within each visit session. The baseline period will be followed by an intervention assessment period of 8 weeks when they are using the dynamic seat, and then a 2 month follow-up period. The duration of the baseline will be randomised for each child and will be between 2 and 7 weeks and therefore participants with longer baselines will have a larger number of baseline data-points. The baseline period will represent treatment as usual (TAU). In this way, comparison of TAU and dynamic seating provision is possible, with each participant acting as their own control.

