### 3.5. Sample Size

In SCED or N-of-1 design with replications across participants, sample (series) size is not based on the power to test group effects using inferential statistics, as each separate trial examines change over time within an individual. This will allow us to determine whether treatment has an effect for an individual. In N-of-1 studies, the number of replications (participants recruited) chosen after the first case is often based on pragmatic grounds related to the known heterogeneity of the clinical sample, and the number of measurements within each time period is based on the likely variability in outcome. It is recommended that N-of-1 plus 3 replications are necessary as a minimum to explore the efficacy of an intervention, but a total of 5 replications is better. Similarly, it is recommended that at least 3 assessment points are measured at baseline. Multiple baseline assessments will be made per child per week during the randomised baseline period that varies between 2 and 7 weeks.

A sample size of 6 will be sufficient to provide information on whether the intervention is effective for individuals, to examine the direction of ‘average treatment effect’ across individuals, and to provide estimates of the within- and between-subject variability of outcomes in this population. It will also allow us to obtain information on ease of recruitment and adherence to protocol.

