### 3.6. Randomisation and Allocation Concealment

Treatment allocation will take place by randomisation with participants of assigned baseline length. Allocation concealment will be achieved by registration of consented participants on to a randomisation database prior to the allocation arm being sent to the principle investigator via email, and from there to the centre delivering treatment.

The trial statistician who has no direct contact with the clinical aspects of the trial or the study team will perform randomisation. Block randomisation will be performed, and a list will be generated using Stata (https://www.stata.com/). The length of each participant’s baseline period will be randomised to a non-repeating sequence of random integer durations that are between 2 and 7 weeks, where 2 weeks ≤ baseline period ≤ 7 weeks.

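### The PQRS data point is defined in two ways, and both count repeats filmed in one weekly visit as separate observations, so precision around Tau-U is overstated if those repeats are correlated.

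*Protocol article*

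**What the plan says.** The protocol article defines the PQRS data point twice.

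- Section 3.1 (Design): "each trial provides one data point or baseline assessment, for example, reaching forward to hit a switch is one data point/one baseline". It adds: "Therefore, there will be multiple baselines within each visit session".
- Section 3.19.1 (Data from SCED): "Therefore, each task step within a task is assigned a data point".

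On timing, Section 3.15 says: "A researcher will visit the child and family once per week to measure goals set up by the family". Section 3.18 also refers to weekly visits, and Table 1 has one PQRS column per week in baseline (b1-b7) and intervention (t1-t8), each marked xxx. Section 3.6 sets the baseline length: "where 2 weeks ≤ baseline period ≤ 7 weeks". The intervention lasts 8 weeks.

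On analysis, Section 3.19.1 names Tau-U as the effect-size approach and justifies it by its handling of baseline trend. It keeps ordinary least squares as a reference fit, leaves the other regression open, and says that the analysis will depend on baseline autocorrelation and serial dependency. Nothing says that points from one visit are averaged or treated as a cluster. No significance level is given for the within-child analysis.

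**The concern.** Attempts and task steps filmed in one session share the day, the child's state and the seat set-up. They are likely to resemble each other more than scores from different weeks do. An analysis that takes them as independent credits the child with more information than the visits supply, and the number of points grows with how finely a task is cut into steps.

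Two stated purposes are exposed. Section 3.5 wants to judge whether treatment works for an individual, which depends on the uncertainty attached to Tau-U. Sections 2.3 and 3.9 want between- and within-period variances, an effect size and a standard deviation to design the next trial. Those quantities change with the unit, and the document gives two units.

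**Working it through.** The plan states no error rate for the within-child analysis, so there is no figure of its own to reproduce.

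**Inputs from the document.** Baseline of 2 to 7 weeks, intervention of 8 weeks, one visit per week. Each child therefore gives 2 + 8 = 10 to 7 + 8 = 15 visits. Reading xxx as three trials is an interpretation, since the Table 1 note explains only X. On that reading, a 2-week baseline gives 2 × 3 = 6 trials from 2 occasions.

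**Assumptions.** Two-sided alpha of 0.05; ICC from 0 to 0.7; 3 points per visit, or 9 (3 trials × 3 steps); no seat effect; visits independent of each other.

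**Formula.** With m points per visit, the design effect is D = 1 + (m − 1) × ICC. A nominal 5% test that ignores it has true size of about 2 × [1 − Φ(1.96/√D)].

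- m = 3, ICC 0.5: D = 1 + 2 × 0.5 = 2.0; 1.96/√2.0 = 1.39; size 16.6%.
- m = 9, ICC 0.3: D = 1 + 8 × 0.3 = 3.4; 1.96/√3.4 = 1.06; size 28.8%.

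**Simulation of Tau-U** with baseline-trend correction, treating points as independent. There were 2,000 runs per setting; the range is over 2, 4 and 7 baseline visits.

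| ICC | m = 3, formula | m = 3, Tau-U | m = 9, formula | m = 9, Tau-U |
|---|---|---|---|---|
| 0 | 5% | about 5% | 5% | about 5% |
| 0.1 | 7.4% | 6-7% | 14.4% | 12-15% |
| 0.3 | 12.1% | 11-12% | 28.8% | 27-30% |
| 0.5 | 16.6% | 15-18% | 38.1% | 39-40% |
| 0.7 | 20.6% | 20-23% | 44.6% | 44-47% |

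Tau without the trend correction gives nearly the same rates, so the correction offers no protection against clustering.

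**Fixed differences between steps.** With 15 points per visit (5 steps × 3 trials) and no step differences, Tau-U rejects in 31-32% of runs at ICC 0.2 and 49-52% at ICC 0.5. With step variance 1 to 2 times the other variance, this falls to 13-20% and 28-37%. At ICC 0 it falls below 5%.

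**One mean per visit.** Type I error is about 4-6% (t-test) and 3-6% (exact Mann-Whitney) at every ICC. With 2 against 8 visits, the smallest exact two-sided p is 2/C(10,2) = 2/45 = 0.044.

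**Variance, as an illustration.** Take visit plus residual variance of 1, ICC 0.5, step variance 1 and m = 15. Single step scores have variance 0.5 + 0.5 + 1 = 2 (SD 1.41). Visit means over the same steps have variance 0.5 + 0.5/15 = 0.533 (SD 0.73). The same child yields an SD that differs by a factor of 1.41/0.73 = 1.9 according to the unit.

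**The case against.** The strongest reply is that this is a feasibility series of six children, not sized on power. Tau-U is offered as an effect size alongside visual analysis, with no stated alpha or decision rule. A full statistical analysis plan is promised, and the analysis is already to respond to serial dependency. Much of this stands. The harm is to stated precision and to variance estimates, not to a confirmatory error rate. But the serial-dependency clause concerns correlation over time, does not name clustering within a visit, and would be checked on as few as two baseline visits. The unit itself is fixed in the article, twice and differently. The conflict may be partly one of terms, since one reach to a switch could itself be a step, but that too needs saying.

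A reader might infer more than the document supports:

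- **That false positives are several times nominal.** This depends on an ICC, a step count and an alpha that the document does not give. With three points per visit and ICC 0.1 the rate is only about 1.3 times nominal.
- **That the regression lacks a visit term.** Ordinary least squares is a reference fit only, and the form of the other regression is left open.
- **That a 2-week baseline misses the protocol's own minimum.** Section 3.1 promises "at least 5 baseline assessments over at least 2 weeks in their usual seating" and defines an assessment as a trial, so six trials meet it. Section 3.5 cites a recommendation of three assessment points, and Section 3.17 asks for three filmed assessments per goal. Neither counts visits.
- **That the 2-7 week range must therefore change.** Defining the unit does not require it; a longer baseline is a separate design trade-off.

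**Conclusion.** The point holds as a defect in how the unit of analysis is fixed. Sections 3.1 and 3.19.1 disagree, and under either definition 10 to 15 weekly visits per child are presented as a larger number of independent points. If within-visit correlation is positive, uncertainty around Tau-U is understated. Under the stated assumptions without step differences, and for ICC 0.1 to 0.7, type I error runs from about 6% to 23% with three points per visit and from about 12% to 47% with nine. It is nominal at ICC 0 and lower where steps differ in fixed difficulty. The mixing of step, trial and visit variation in the estimates for the future trial does not depend on any alpha. The direction is secure once the correlation is positive; the size is not known from the document.

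**What to change.** State one definition of the PQRS data point in Sections 3.1, 3.17 and 3.19.1. Use one value per goal per visit (the mean over trials and steps) for Tau-U and the phase plots, or fit a model with a random effect for visit. Report the number of visits per phase beside any trial or step counts, and report between-visit and within-visit variance separately for the design of the next trial.

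The cost is wording and fewer nominal data points; filming and rating do not change. The child with a 2-week baseline would have only two baseline points, where the smallest attainable exact p is 0.044, so a visit-level comparison for that child has little sensitivity. Visit means remove within-visit clustering but not autocorrelation between visits, which the simulation did not include, so the existing serial-dependency check should stay and be applied at visit level.
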